## Results

The RCT is ongoing. We have contacted 294 potential participants and recruited 44 to this moment. Recruitment will close in April 2024. We plan to complete data analyses by December 2024.

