### Setting and Participants

Treatment is offered at CHULN Lisboa Norte to family members or other caregivers of patients, followed by the palliative care unit and oncology service. Inclusion criteria involve individuals more than 18 years old, having experienced the death of a close person (e.g., relative, partner, friend) due to cancer in a palliative or oncological context from three to 12 months, and sufficient cognitive abilities and proficiency in the Portuguese language who provide written informed consent. Participants are invited from the service registry, where the reference caregiver is identified. Exclusion criteria include individuals reporting a diagnosis of pre-existing severe or active mental disorder predating the loss (e.g., schizophrenia, bipolar disorder, major depression). Participants currently undergoing psychological intervention will also be excluded. While medication will be monitored, it will not be an exclusion criterion.

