### Treatment Conditions

#### TAU

Treatment as usual (TAU) consists of supportive psychotherapy based on a non-structured and integrative method that focuses on developing more adaptive coping strategies and understanding and working on the patient's internal models of self, others, and the world (Winston & Lujack, 2015). For the present investigation, TAU will be considered during the same period as the Empower-Grief intervention – that is, 12 weeks – as the frequency of sessions may differ slightly from case to case. Psychologists with specific training for each intervention will administer both interventions.

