### Assessments and Instruments

Three measurement points will be considered (Table 1). Considering the context of data gathering, care has been taken to avoid overburdening participants with excessive questionnaires. The screening will include sociodemographic data and RAG. The first assessment, before the first session, includes some additional sociodemographics, PG13-R, HADS, Brief COPE, ECR-RS, AAQ-II, and MSPSS. The second assessment will include PG13-R, HADS and the working alliance measure (WAI-S). The follow-up assessment period (3rd assessment) will occur six months after the last assessment. These will include all outcomes (PG13-R, HADS, PTGI). The interventions will share the same assessment periods and instruments. The follow-up assessment ensures that all participants are evaluated one year after the death, enabling a PGD diagnosis.

**Table 1 t1:** Time Points for Measurement

Instrument	Screening	T1	T2	6 mths
Sociodemographics	x	x		
Risk Assessment for Grief (RAG)	x			
PG-13-R		x	x	x
The Hospital Anxiety and Depression Scale (HADS)		x	x	x
The Posttraumatic Growth Inventory (PTGI)				x
Brief COPE		x		
Experiences in Close Relationships (ECR-RS)		x		
Acceptance and Action Questionnaire II (AAQ-II)		x		
The Multidimensional Scale of Perceived Social Support (MSPSS)		x		
The Working Alliance Inventory-short form (WAI-S)			x	

*Note*. T1 = Pre-treatment; T2 = 12 weeks/Post-treatment; 6 months = follow up.

Participants will be contacted sensitively to inquire about the reasons for discontinuing the intervention. Clinical teams will receive supervision for each intervention, and adherence to treatment measures will be monitored.

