#### Primary Outcome

##### Prolonged Grief Scale – Revised (PG13-R)

The PG13-R is a self-report scale developed by Prigerson and colleagues (Prigerson et al., 2021) based on DSM-5-TR criteria for PGD. PG-13-R includes 13 items, evaluated on a 5-point Likert scale. PG-13-R grief symptoms represent a unidimensional construct with high degrees of internal consistency in research conducted at Yale (Cronbach's α = .83), Utrecht (Cronbach's α = .90), and Oxford (Cronbach's α = .93) universities. PGD diagnosis is attributed when the person obtains a total value greater than 30 and meets the temporal (12 months) and impairment criteria.

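### The third assessment falls about a week short of the promised one-year mark for the earliest entrants, and for most April 2024 entrants it falls after the planned end of analysis; a minor consistency correction

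*Protocol article*

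**What the plan says.** Four parts of the protocol article bear on the timing of the third assessment.

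- **Entry.** Under Setting and Participants, the death must have occurred "in a palliative or oncological context from three to 12 months" earlier.
- **Visit schedule.** Under Assessments and Instruments, T1 is "The first assessment, before the first session", and the note to Table 1 reads "T2 = 12 weeks/Post-treatment; 6 months = follow up". The text adds: "The follow-up assessment period (3rd assessment) will occur six months after the last assessment". The TAU section gives the same treatment period for both arms: "TAU will be considered during the same period as the Empower-Grief intervention – that is, 12 weeks".
- **One-year guarantee.** Assessments and Instruments also states: "The follow-up assessment ensures that all participants are evaluated one year after the death, enabling a PGD diagnosis". The section on the PG13-R explains why this matters: a diagnosis requires a score above 30 in a person who also "meets the temporal (12 months) and impairment criteria".
- **Calendar.** The Results section says: "Recruitment will close in April 2024. We plan to complete data analyses by December 2024". It also reports that 44 participants had been recruited when the article was written, which equals the target sample size.

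**The concern.** The article gives the intervals and the dates, and it also makes two claims that should follow from them: that everyone is seen at one year or later, and that the analyses can be finished in December 2024. Adding up the intervals supports neither claim for every permitted participant.

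On the first, a participant seen before 12 months cannot be given a PGD diagnosis whatever the symptom score, so the diagnostic status of that participant at the last visit would be undefined or negative by timing alone. On the second, the third assessment is one of the three time points in the primary mixed model (Statistical Analysis). An analysis completed before the last of these visits would lack part of the data it is meant to use.

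**Working it through.** **Inputs.** Minimum time from death to entry: 3 months (Setting and Participants). T1 to T2: 12 weeks = 84 days (Table 1 note; TAU). T2 to third assessment: 6 months (Assessments and Instruments). Diagnostic threshold: 12 months (PG13-R). Recruitment closes: April 2024. Analyses complete: by December 2024 (Results). Assumption: no lag between entry and T1.

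**1. Time since death at the third assessment**

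Time since death = time to T1 + 84 days + 6 months.

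- In average months of 30.4375 days: 3 + 84/30.4375 + 6 = 3 + 2.76 + 6 = 11.76 months. The shortfall is 0.24 months, or about 7 days.
- By calendar, with a death on 1 January 2023 as an example: T1 on 1 April, T2 on 24 June, third assessment on 24 December 2023. Twelve months is reached on 1 January 2024, so the visit is 8 days early.
- Over all death dates from June 2022 to January 2024, the shortfall is 5 to 9 days, with a mean of about 7.
- T1 must therefore come at least 12 − 6 − 2.76 = 3.24 months after the death. A T1 about 9 days or more past the three-month point removes the gap for every death date tried.

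**2. Calendar date of the third assessment**

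Third assessment = T1 + 84 days + 6 months.

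| T1 | T2 | Third assessment |
|---|---|---|
| 1 April 2024 | 24 June 2024 | 24 December 2024 |
| 7 April 2024 | 30 June 2024 | 30 December 2024 |
| 8 April 2024 | 1 July 2024 | 1 January 2025 |
| 30 April 2024 | 23 July 2024 | 23 January 2025 |

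If December is read generously as 31 December, 7 of the 30 April start dates give a visit in the last week of the year and 23 give one in January 2025. If it is read as 1 December, T1 would have to be no later than 9 March 2024. Neither limit allows time for data cleaning or modelling.

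**3. Other readings of the T1–T2 interval**

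- Three calendar months: 3 + 3 + 6 = 12, so the one-year gap closes, but T1 on 30 April then leads to 30 January 2025.
- Six weeks: T1 on 30 April leads to 11 December 2024, but the one-year gap grows to 47 to 51 days.

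Of the readings tried, none satisfies both statements with time left to analyse.

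**The case against.** The dates are not in dispute. The objection is that little follows from them, and most of it stands.

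- **Missing follow-up data.** A reader might infer that late entrants' final scores would be missing by calendar and filled by multiple imputation. The documents do not say so. The December date is a forecast in a status paragraph and sets no data lock, and the imputation plan does not extend to visits that are not yet due. The ordinary result of a tight forecast is that the analysis slips by some weeks.
- **Number affected.** With the target of 44 already reached, there may be few or no participants with T1 after 7 April. Recruitment was still open until April, so the plan allows them, but none is shown. Nor do all April entrants pass year-end: those of 1 to 7 April do not.
- **Under-counted PGD.** A reader might infer that PGD at follow-up is under-counted in a way that affects the results. The Statistical Analysis section uses prolonged grief severity as a continuous outcome, with anxiety and depression as secondary outcomes, and includes no analysis of PGD diagnosis. A symptom score taken a week before the anniversary is fully usable.
- **Rounding.** The gap arises from counting 12 weeks as 84 days beside calendar months. Phone contact, screening, consent and randomization precede the first session, so if the three-month criterion is judged early in that sequence, a lag of about 9 days closes the gap. The article does not say when it is judged. The same lag moves the calendar dates later.
- **Wider gap.** A reader might take the Abstract, which counts follow-up from the intervention, to imply a larger shortfall. The article gives 12 weeks for both arms and equates T2 with post-treatment, so this is not supported.

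What survives is narrower: the article guarantees the one-year point for all participants and gives a completion date, and its own intervals deliver neither for everyone it permits to enter.

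**Conclusion.** The point holds as a minor inconsistency among the entry window, the visit schedule, the diagnostic time criterion and the calendar. No bias in the primary comparison has been shown.

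The one-year guarantee fails by about a week, and only for participants whose T1 falls within roughly 9 days of the three-month limit. The completion date fails by up to 23 days past year-end, before any analysis time, for T1 after 7 April 2024, and leaves no working time for T1 on 1 to 7 April.

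Both results take 12 weeks as 84 days. The first also assumes that the three-month limit can coincide with T1. The second assumes that some participants start in April, which the plan permits but the article does not show.

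**What to change.** - **One-year point.** Either schedule the third assessment at the later of six months after T2 and 12 months after the death, or keep the schedule and derive PGD diagnosis only from assessments at or after 12 months. In both cases, reword the sentence that guarantees the one-year point for all participants. The first option costs a delay of 5 to 9 days for visits at the three-month limit, and less for those slightly beyond it. The second moves no visits, but the few seen early would have no diagnosis derived from that visit.
- **Analysis date.** State that the final analysis follows the last scheduled third assessment, and move the date accordingly. If recruitment ran to 30 April 2024, that visit falls on 23 January 2025, so the delay is about one to two months including time to clean and analyse. If the last T1 was earlier, give that date and the delay shrinks or disappears.

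Neither change affects the model, the sample size or the primary outcome.

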## Discussion

This study responds to a lack of research in grief interventions, which is relevant considering the high prevalence of PGD and the general delay in providing care. Assessing the differentiation of intervention leads to increases and equality in access to empirically based interventions. By empowering caregivers to respond to a challenging grief process, the intervention may contribute to preventing pathological long-term psychological reactions. The present research project aims to assess the efficacy of a low-intensity selective intervention compared with TAU in terms of prolonged grief symptoms and distress. The project's second goal is to identify potential predictors of the outcome and adherence to these treatments – considering the matching conditions.

This research has several strengths. First, the study of low-intensity interventions – recommended by international and national bodies (Shear et al., 2017) – has a good cost-benefit ratio and increases access to psychological interventions in this social context. Second, Empower-Grief is flexibly delivered so that it can be adapted to caregivers’ dynamic needs and post-mortem context. Third, it was developed and refined using stakeholder feedback to optimize its acceptability and fit for its recipients’ specific needs. Also, identifying predictors of adherence and change serves to increase sensitivity in aligning interventions to the needs of clients.

The fact that the current study is conducted in a practice setting leads to some constraints – namely, the lack of manualization of TAU or the need to keep the research questionnaire relatively small. However, the practice-based nature of the context of data gathering provides a demonstration of how a structured intervention such as Empower-Grief can be useful. Results from this study will, therefore, provide a pathway for improving clinical decision-making and tailoring treatments to an individual's specific needs, which is crucial to meeting citizens’ needs in the context of the rational provision of services.

This research is situated in the field of intervention personalization and psychological services research. It can inform and enrich the predicting process by considering other dimensions of patient characteristics, such as psychological flexibility or attachment, thus fostering new research and informing bereavement support practice.
